### Study analysis (begins at end of recruitment month 43)

#### Enrollment summary and comparison of participants at baseline

We will report on participant enrollment and summarize the reasons for accepting or declining enrollment or drop-out from the study using the Consolidated Standards of Reporting Trials (CONSORT) approach [62]. We will summarize the demographic characteristics, HIV testing history, and health literacy level (measured by the SAHL-S&E [22] and brief instruments) using conventional statistics, such as means/standard deviations, medians/ranges, or counts/frequencies with corresponding 95% confidence intervals (CIs), as appropriate. For Latino participants, we will summarize nativity and US acculturation (measured by the SASH [63, 64]) in a similar manner. We will summarize these baseline characteristics for all participants and as stratified by informational delivery mode (pictorial brochure or video), language preference (English or Spanish), and health literacy level (lower or higher). Next, we will compare the baseline characteristics of study participants between the study arms using Pearson’s Χ^2^ or Fisher’s exact test for categorical variables and Student’s t-test for normally distributed or Wilcoxon’s rank-sum test for non-normally distributed continuous variables to assess the success of the randomization procedure. Any chance imbalances between the two arms will be documented and investigated, and will be adjusted for by including the imbalanced covariate as an independent variable in our subsequent regression analyses, or through a weighted analysis using a propensity score (propensity to be enrolled in the study with weights equal to the inverse of the propensity score) [65]. A two-tailed, *α = 0.05* significance level will be used for all analyses.

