#### Information delivery and post-information delivery questionnaires

We will randomly assign patients in a 1:1 ratio into information delivery mode Arm 1 or Arm 2. As noted previously, the two arms will be stratified within language (English or Spanish) and health literacy level [22] (lower vs. higher) (*n* = 150/stratum). We will use block randomization techniques to ensure that there are equal numbers in each arm per study site and stratum using a centralized, random assignment computerized system. Randomization sequences by language and health literacy level will be posted on a secure website that RAs across all four sites will consult when assigning participants to study arms. The advantage of this approach is that we can monitor enrollment and balance within study arms and across study sites easily, address concerns as they arise, and permit efficient use of study resources. The two groups will differ by the following:Arm (1): HIV/AIDS and HIV testing video: Participants in Arm 1 will watch the video, “What do you know about HIV and HIV testing?” (in English or Spanish) on a tablet computer in the ED while the RA waits. They will listen to the audio components using disposable headphones.Arm (2): HIV/AIDS and HIV testing pictorial brochure: Participants in Arm 2 will be provided with a copy of our HIV/AIDS and HIV testing pictorial brochure (in English or Spanish) to review in the ED. Arm 2 participants will read the brochure while the RA waits. The RAs will not provide clarifications or assistance with the information in the pictorial brochure.

After watching the video or reviewing the pictorial brochure, all patients will complete the post-information questionnaires using the automated telephone key-pad response system (the HIV risk self-perception and value of HIV testing, HIV/AIDS and HIV testing information delivery mode preferences and satisfaction, the HIV/AIDS and HIV testing knowledge, and the HIV risk-taking questionnaires). Patients will receive a re-chargeable gift card for participating.

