#### Sample size considerations

The study sample size is *n* = 1200, with equal size strata (*n* = 150) by language, health literacy level, and information delivery mode (Fig. 4). This sample size is based on a 2x2x2 full factorial design and will satisfy the requirements for analysis of the two primary aims and the four alternative hypotheses paired with each aim. The minimum sample size is calculated for a power of 0.80 and a two-sided *α = 0.05* level of significance (Table 3). In general, a larger sample size is needed for greater variation of scores within study arms and strata, lower within-person correlations of scores, and higher loss-to-follow-up. To maximize power, we chose conservative values based upon our prior studies. We increased the sample size by 20% to account for the heterogeneity in patients among the four study sites, and by a conservative additional 25% to account for possible attrition. Based upon other 12-month ED intervention follow-up studies [10], HIV/STD testing studies [57–59], and studies conducted at our own ED [60, 61], a 25% attrition rate at 12 months likely is a worst-case scenario. We expect that our experience and enhanced measures to encourage and facilitate follow-up will result in higher follow-up rates. As of publication of this manuscript, 1165 participants enrolled completed the three-month follow-up.

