**Fig. 4 Fig4:**

Sample size by study arm, language, and health literacy level

**Table 3 Tab3:** Sample size rationale by primary aims

Primary Aims	Minimum sample by stratum	Total minimum sample	Rationale and assumptions for minimum sample sizes and final sample sizes for each primary aim
Aim 1. Short-term improvement in HIV/AIDS and HIV testing knowledge ** HA1**: 3-way interaction (mode*language*literacy level) ** HA2**: 2-way interaction (mode*language or literacy level) ** HA3**: no interaction (difference by mode only) ** HA4**: no difference	**125** This **minimum** sample size by stratum will yield a power of 0.80, 0.97 and 0.99 for testing HA1, HA2, HA3 versus HA4 (HA4 as the NULL) Final sample per stratum (information delivery mode, language, and health literacy level) is 150	**1000** The **final sample** after adding 20% to account for the heterogeneity in patients among study sites is **1200** = 1000*(1 + 20%)	• Based on our prior video studies [17, 19, 21], we assume that the scores on the 25-item questionnaire is a normal distribution with a standard deviation of ~ 3 • Before information delivery, mean scores of the two arms are assumed to be the same (due to random assignment) per stratum • Short-term within-person correlation is 0.7 or higher [21] • The pictorial brochure will improve knowledge by an average of 2 points. The video will improve the knowledge by an average of 3.5 points. The effect size is Δ = 3.5–2 = 1.5. (HA3) • 2-way intrxn (mode*language or literacy level) effect size is Δ = 1.5 + 0.75 = 2.25. (HA2), e.g. for those speaking English OR with high health literacy • 3-way intrxn (mode*language*literacy level) effect size is Δ = 1.5 + 0.75 + 0.75 = 3.0, e.g. for those speaking English AND having high literacy AND watching the video

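### Inverse weighting by the propensity to be enrolled is offered as a remedy for chance imbalance between the randomised arms, but that score is for the wrong event and cannot remove such an imbalance

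*Protocol article*

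**What the plan says.** All of the text at issue stands in the protocol article under Enrollment summary and comparison of participants at baseline.

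- Baseline characteristics are to be tested between arms with chi-square or Fisher tests and t or rank-sum tests. The stated purpose is "to assess the success of the randomization procedure".
- The next sentence says: "Any chance imbalances between the two arms will be documented and investigated".
- The first remedy is that the imbalance "will be adjusted for by including the imbalanced covariate as an independent variable in our subsequent regression analyses".
- The second, joined by an *or*, is a weighted analysis using a propensity score, defined in brackets as the "propensity to be enrolled in the study with weights equal to the inverse of the propensity score".
- A two-tailed 0.05 "significance level will be used for all analyses".

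Nothing in the section chooses between the two remedies, and no measure of imbalance other than the tests is named.

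The Primary aims analysis section separately plans models with covariates, independent of any baseline test. For Aim 1 these are demographic characteristics and covariates that are important or were used in stratification. Language and literacy are in the linear predictor, and the pre-information score is the first of the two repeated outcomes. For Aim 2 they are language, literacy, age, gender and others.

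**The concern.** The problem to be solved is a chance difference between two randomised arms. The tool named for it is a score for a different event. An analyst who followed the text would estimate the probability of enrolment, weight by its inverse and report an analysis as corrected for imbalance when it is not. That analysis could also be less precise than the unweighted one and refer to a different population.

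A lesser issue sits beside it. The tests, the adjustment sentence and the general 0.05 level follow one another, so an analyst could let baseline p-values decide which covariates enter and could choose between regression and weighting after seeing the data. Under sound randomisation the tests examine a null hypothesis that is true by design. They are therefore a poor way to find the covariates that matter for the outcome.

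**Working it through.** **The plan's own figure.** The only figure that bears on this is the sample size. Table 3 gives 1000 × 1.20 = 1200 for Aim 1 and 800 × 1.25 × 1.20 = 1200 for Aim 2, and both reproduce. Assignment is 1:1 ("We will randomly assign patients in a 1:1 ratio into information delivery mode Arm 1 or Arm 2"), which gives 600 per arm. "Final sample per stratum (information delivery mode, language, and health literacy level) is 150", which gives 150 per arm within each combination of language and literacy. Table 3 also supplies a score SD of about 3, a short-term within-person correlation of 0.7 and an arm effect of 1.5 points.

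**Step 1: what the weights do.** The documents use enrolment in two senses.

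- *Recruitment from the ED.* Among randomised participants the weight 1/P(enrolled | X) is the same function of X in both arms. It moves both arms toward the screened population, and nothing in it pulls one arm's mean of X toward the other's.
- *Entry to follow-up.* Under Follow-up assessments, patients are invited to enrol after assignment, information delivery and a negative HIV test. Inverse weights would then address selection into follow-up. They would aim to restore the randomised group, including whatever chance imbalance it had.

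Arm-assignment weights are 1/P(arm 1 | X) in arm 1 and 1/(1 − P(arm 1 | X)) in arm 2. Fitted to the realised assignment, they act in opposite directions in the two arms and bring both to a common distribution of X.

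**Step 2: simulation of the recruitment reading.** There were 2000 trials, each with 2400 patients screened and about 1200 enrolled and randomised 1:1. From Table 3: SD 3 and effect 1.5. Assumed, and not in the documents: the pool of 2400, one covariate with log-odds 0.8 per SD for enrolment, and a correlation of 0.5 with the outcome.

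| Method | Mean absolute imbalance (SD) | SD of estimate (points) |
|---|---|---|
| Unadjusted | 0.047 | 0.172 |
| Enrolment weights | 0.063 | 0.200 |
| Arm-assignment weights | 0.0001 | 0.149 |
| Analysis of covariance, always | not applicable | 0.149 |
| Analysis of covariance only if baseline p < 0.05 | not applicable | 0.166 |

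Two entries can be checked by hand. The unadjusted SD should be 3 × √(2/600) = 0.173. With adjustment it should be 0.173 × √(1 − 0.5²) = 0.150. Both agree with the table.

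In the 98 trials with a significant imbalance, bias in the direction of the imbalance was 0.20 points unadjusted, 0.22 with enrolment weights, and about 0 with arm-assignment weights or analysis of covariance.

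**Step 3: the baseline tests.**

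- The chance of at least one p < 0.05 among k independent tests under sound randomisation is 1 − 0.95^k. That is 23% for k = 5, 40% for k = 10 and 54% for k = 15. The number of variables is an assumption.
- The largest difference that stays non-significant is 1.96 × √(2/600) = 0.113 SD overall and 1.96 × √(2/150) = 0.226 SD within a stratum. For a knowledge score with SD 3 these are 0.34 and 0.68 points.
- The section plans comparisons of pre-to-post change. An imbalance in the pre-information score shifts a change-score comparison by (correlation − 1) × imbalance: (0.7 − 1) × 0.34 = −0.10 and (0.7 − 1) × 0.68 = −0.20 points. The sign is opposite to the imbalance.

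**The case against.** The faulty definition is a single parenthesis, it accompanies a citation that could not be consulted, and it may be a slip for the propensity of arm assignment. It is one of two options, and the other is sound. All of this stands, and it limits the consequence. It does not make the printed rule correct, because an analyst who applied it as written would use the wrong weights.

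A reader might go further and infer that selecting covariates by test leaves prognostic imbalance unadjusted in the primary analysis. The documents do not support that. The Primary aims analysis section puts covariates into the models whatever the tests show, as set out above. The adjustment sentence speaks of any chance imbalance and does not confine itself to significant ones, so a 0.05 trigger is a plausible inference and not a stated rule. That the covariates are not itemised is something a journal article may leave to the full plan.

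A reader might also carry a pre-information imbalance straight into a comparison of post-information scores and obtain a larger bias. No unadjusted post-score comparison is planned; the change-score figures in the working are the relevant ones.

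Finally, a reader might argue simply that enrolment precedes randomisation. The protocol is not consistent on this, since it also uses the word for entry to follow-up after assignment. The conclusion holds under both uses, so it does not depend on that argument.

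**Conclusion.** The weighting clause is wrong for its stated purpose under either meaning of enrolment. That conclusion rests on reasoning and not on the simulation. The simulated sizes (imbalance 0.047 SD becoming 0.063, SD of the estimate 0.172 becoming 0.200) depend on the assumed enrolment and outcome associations and are illustrative only.

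Using baseline tests to decide adjustment is poor practice, and the text invites it without quite prescribing it. Its effect here is limited. A non-significant imbalance in the pre-information score moves the planned change-score comparisons by about 0.1 points overall or 0.2 within a stratum, against the planned 1.5. Test-based selection also gives up some precision compared with adjusting in every case (0.166 against 0.149, same assumptions), and only for covariates not already in the models.

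**What to change.** 1. Delete the propensity-weighting clause, or redefine the score as the propensity of arm assignment and keep the weighted analysis as a sensitivity analysis only.
2. Present the baseline tables descriptively, and state that between-arm baseline tests do not determine adjustment.
3. State that the prognostic and stratification covariates already foreseen under Primary aims analysis enter irrespective of baseline p-values.
4. Enter site within language. Under Study sites and recruitment feasibility, Spanish speakers are recruited in Los Angeles and Providence and English speakers in Birmingham and Cincinnati. Four unrestricted fixed site effects would therefore be aliased with the language main effect.

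The cost is a few sentences in the analysis section. No new data, and no change to design or sample size, are needed.

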#### Primary aims analysis

For Aim 1, we expect that HIV/AIDS and HIV testing knowledge scores can be reasonably approximated by a normal distribution (Table 4). We will compare differences in pre- vs. post- changes in scores between information delivery modes by paired t-tests. If the data are not normally distributed, we will use signed-rank tests. All tests will be executed on an intention-to-treat basis (non-adherence to assigned information delivery mode likely is minimal). Comparisons will first be made for each stratum. MANOVA/ANCOVA will be used for combined samples where language and literacy level are used as stratifying (main) factors. To further account for baseline covariates (e.g., demographic characteristics), a generalized linear mixed-effect model will be fit to the data. The parameters of interest are the coefficients of the dummy variable indicator of study arm assignment and its interactions with language and health literacy level.

**Table 4 Tab4:** Analyses of primary aims

Primary aims	Measurements	Analytic methods
Aim 1. Short-term improvement in HIV/AIDS and HIV testing knowledge **HA1**: 3-way interaction (mode*language*literacy level) **HA2**: 2-way interaction (mode*language or literacy level) **HA3**: no interaction (difference by mode only) **HA4**: no difference	HIV/AIDS and HIV testing knowledge questionnaire at baseline in ED at time of HIV testing, post- vs. pre-information delivery	• Paired t-tests • Signed-rank tests • MANOVA/ANCOVA • Generalized linear mixed-effects regression
Aim 2. Retention of HIV/AIDS and HIV testing knowledge at 3, 6, 9, and 12 months **HA1**: 3-way interaction (mode*language*literacy level) **HA2**: 2-way interaction (mode*language or literacy level) **HA3**: no interaction (difference by mode only) **HA4**: no difference	HIV/AIDS and HIV testing knowledge questionnaire at 3, 6, 9, and 12 months vs. baseline (post-information delivery)	• Paired t-test for each follow-up vs. baseline • Linear mixed-effects regression (assuming constant degradation over time) • Broken-stick linear mixed-effects regression (for non-constant degradation over time)

The generalized linear mixed-effect model will be structured as follows: *Y*^***^_*ij*_ *= α*_*j*_ *+ f(R*_*i*_*,LG*_*i*_*,LT*_*i*_*; β) +* μ_i_ *+ θX*_*i*_*,* where *j = 0,1* indicates pre- and post-information, *Y*^***^_*ij*_ is the outcome of subject *i*, R_i_ indicates the arm assignment, *α*_*j*_ is the intercept (*α*_*0*_ being the pre-information value for j = 0; and *α*_*1*_ the post-information value for j = 1), *β* is a vector that captures the main effects, and 2- and 3-way interactions among information delivery mode *(R),* language *(LG*), and literacy *(LT)*, *f* () is a linear predictor function, and *X*_*i*_ contains important or stratification covariates, with *θ*θ being their effects. For this unified approach, *Y*_*ij*_^***^ = *g*[E (*Y*_*ij*_)] where *g*() is an appropriate transformation of the outcome being analyzed. For example, for continuous outcomes, *g*() can be an identify link; for count or binary outcomes (as in the exploratory aims), *g*() can be a log or logit/probit transformation. We will assume that *u*_*i*_
*~ N(0, τ*^*2*^*)*, which is a random effect that captures the within-subject correlation of the repeated measurements. We will fit the models using the restricted maximum likelihood method, or generalized estimating equations (GEE) if non-identify links are used.

For Aim 2, we will first compare the baseline literacy scores at each of the follow-up visits to the baseline score (post-information delivery) using paired *t*-tests. If the retention of HIV/AIDS and HIV testing knowledge demonstrates a linear trend over time, we will fit a linear mixed-effect model to the combined data, in which independent variables will include time, information delivery mode, language and baseline health literacy level; their interactions; age, gender, etc. If the trend is not linear, we will consider fitting a broken-stick (piecewise linear) linear mixed-effect model. The parameters of interests are the coefficients of time, indicating follow-up assessments, and the interactions of time and study arm assignment, information delivery mode and language.

If a linear assumption is supported by data, the linear predictor in the above model will be expressed as *α*_*0*_ *+ β*_*1*_*[time] + β*_*2*_*[time]*R*_*i*_*[mode]*, where *β*_*1*_ and *β*_*2*_ capture HIV/AIDS and HIV testing knowledge retention rate over time and the difference in the rate between two delivery modes. We will further evaluate the 2- and 3-way interactions *β*_*2*_*[time]*[language]*R*_*i*_
*[mode]* and *β*_*2*_*[time]*[health literacy level]*R*_*i*_*[mode]* and possibly (if data allow) 4-way interactions *β*_*2*_*[time]*[language]*[health literacy level]*R*_*i*_*[mode]*, to investigate the interaction of information delivery mode with language and health literacy and whether one delivery model works better in certain sub-groups. Our analysis by time will permit us to determine if and when HIV/AIDS and HIV testing knowledge degrades, and if and when knowledge reaches baseline pre-information levels (i.e., before an intervention), which would suggest a need for repeat delivery of this information at subsequent HIV testing encounters within 12 months. We also will determine if degradation varies by information delivery mode, language, and health literacy level. We recognized that there is no established minimum standard for what level of HIV/AIDS and HIV testing knowledge is necessary or desired; however, we believe that it should be at least greater than pre-information knowledge levels, and will plan the analyses accordingly.

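### Aim 1 names paired tests for comparing two independent arms, and its mixed model has no arm-by-time term, so the named arm parameters equal half the effect on improvement

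*Protocol article*

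**What the plan says.** The protocol article, under Information delivery and post-information delivery questionnaires, assigns each patient 1:1 to video or brochure. Aim 1 asks how improvement from before to after the information differs by mode, language and health literacy.

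Under Primary aims analysis, the first method is: "We will compare differences in pre- vs. post- changes in scores between information delivery modes by paired t-tests". Signed-rank tests are the fallback for non-normal data. Stratum-level comparisons come first, then MANOVA/ANCOVA on the combined sample, then a generalized linear mixed model to account for baseline covariates. Directly after introducing that model the text says: "The parameters of interest are the coefficients of the dummy variable indicator of study arm assignment and its interactions with language and health literacy level".

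The model is then written out. The outcome is indexed by j = 0 (pre) and j = 1 (post). The index j appears only on the intercept α_j. The predictor f takes arm, language and literacy as arguments, and its β "is a vector that captures the main effects, and 2- and 3-way interactions among information delivery mode", language and literacy. Neither f nor β carries a time index.

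Under Enrollment summary and comparison of participants at baseline, one of two options for chance imbalance between arms is weighting by a propensity described as "propensity to be enrolled in the study with weights equal to the inverse of the propensity score".

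**The concern.** Aim 1 is a primary aim, and its target is a difference between arms in change.

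A paired test needs a pairing. The patients in the two arms are different people and are not matched, so a paired or signed-rank test of one arm's changes against the other's has no basis. If the sentence means pre/post tests within each arm, it does not compare the modes.

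The mixed model forces the arm effect to be the same before and after the information. No arm effect can exist before the information, so the fitted coefficient blends a structural zero with the effect of interest. The same applies to the arm-by-language and arm-by-literacy coefficients, which decide HA1 and HA2. Anyone following the equation would report a mode effect of half its true size, with reduced power for the stratum comparisons and interactions.

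**Working it through.** **Inputs** (Sample size considerations and Table 3): "The minimum sample size is calculated for a power of 0.80"; "two-sided *α = 0.05* level of significance"; "normal distribution with a standard deviation of ~ 3"; "Short-term within-person correlation is 0.7 or higher"; equal pre-information means in the two arms; gains of 2 (brochure) and 3.5 (video), so a mode effect of 1.5; minimum 125 per cell in eight cells.

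**Standard deviations**
- ANCOVA residual: 3·√(1 − 0.7²) = 2.142
- Change score: 3·√(2(1 − 0.7)) = 2.324
- Mean of pre and post: 3·√((1 + 0.7)/2) = 2.766

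**Power** is Φ(Δ/SE − 1.96). SE = SD·√(2/n) for two cells of n, SD·√(4/n) for a two-way contrast over four cells, and SD·√(8/n) for a three-way contrast over eight.

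**The plan's own figures.** Table 3 states 0.80, 0.97 and 0.99 for HA1, HA2 and HA3. With SD 2.142 and Δ = 1.5 in each contrast:
- three-way: 1.5/(2.142·√(8/125)) = 1.5/0.542 = 2.77, power 0.790
- two-way, four cells of 125: 1.5/0.383 = 3.91, power 0.975
- two cells of 125: 1.5/0.271 = 5.54, power above 0.999

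The change-score SD gives 0.723, 0.950 and 0.999; the unadjusted SD of 3 gives 0.507, 0.798 and 0.977. The stated figures therefore fit a baseline-adjusted analysis.

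**What the written mixed model estimates.** With two scores per patient and no arm-by-time term, the arm coefficient is the arm difference in patients' pre/post means: (0 + 1.5)/2 = 0.75, with SD 2.766. Simulation of the balanced-data estimators (20,000 runs, 125 per arm) gave a mean of 0.753 and power 0.575. The difference in change gave 1.501 and 0.999. A short check with REML fits (25 runs) gave 0.76 without and 1.50 with the arm-by-time term.

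**Power under the written model against ANCOVA**

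| True contrast | Cells | Model as written | ANCOVA |
|---|---|---|---|
| Mode within a stratum, 1.5 | 2 × 125 | 0.75/0.350 = 2.14; 0.57 | >0.99 |
| Two-way, 1.5 | 4 × 125 | 0.75/0.495 = 1.52; 0.33 | 0.975 |
| Two-way, 1.5 | 4 × 250 | 0.75/0.350 = 2.14; 0.57 | >0.99 |
| Two-way, 0.75 | 4 × 250 | 0.375/0.350 = 1.07; 0.19 | 0.79 |
| Three-way, 1.5 | 8 × 125 | 0.75/0.700 = 1.07; 0.19 | 0.79 |
| Pooled mode effect, 1.5 | 2 × 500 | 0.75/0.175 = 4.29; 0.99 | >0.99 |

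Several contrasts are shown because Table 3 does not fix one. It lists 2.25 for HA2, which is 1.5 plus an increment of 0.75, while its stated power reproduces with 1.5 throughout. Four cells of 250 means averaging over the third factor.

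**Within-arm reading of the paired tests.** At 125 per cell, SE = 2.324/√125 = 0.208. Expected t is 2/0.208 = 9.6 for brochure and 3.5/0.208 = 16.8 for video. Under the plan's assumptions both arms would be significant in every stratum, which says nothing about the difference between modes.

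**The case against.** The strongest reply is that the plan already contains a suitable method. MANOVA/ANCOVA is named in the text and in Table 4 for Aim 1, with post- versus pre-information scores as the measurement. A reader might infer from the paired tests and the equation that no Aim 1 method can estimate the difference in improvement. The document does not support that: an ANCOVA of post score on pre score and arm would estimate the 1.5. An article may leave such model detail to a fuller document. What remains is that the text gives the ANCOVA no arm term or pre-score covariate, mentions only language and literacy as its factors, and appears to place the parameters of interest in the mixed model.

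A second reply is that the equation is a template: it is called a unified approach, and the Aim 2 text rewrites the linear predictor of the same model with time-by-mode terms. This makes a slip of notation plausible. But those terms are written for Aim 2 only. For Aim 1 the arguments of f are listed and the parameters are named, and neither includes time.

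Third, the size depends on the contrast. The 0.19 for a two-way interaction arises only if the contrast is 0.75; with 1.5 it is 0.33 to 0.57. The pooled mode effect loses almost no power. Both points stand.

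A reader might also infer that covariates are chosen solely by baseline significance tests. The text also names demographic characteristics and important or stratification covariates, so that inference fails. The enrolment-propensity wording sits in a sentence about imbalance between arms and may be a slip; it is a side correction only.

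**Conclusion.** Two stated elements of the Aim 1 analysis are wrong as written: paired or signed-rank tests for a comparison of independent arms, and a mixed model whose named parameters equal half the effect on improvement (0.75 instead of 1.5). The halving is exact when pre-information means are equal, as the protocol assumes, and every patient has both scores. The power figures rest on SD 3, correlation 0.7, two-sided 0.05, 125 per cell and a normal approximation.

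The harm is a halved estimate throughout, and weak power for stratum comparisons (0.57) and interactions (0.19 to 0.57, depending on the contrast). The model error does not create false positives for mode: with no true effect the coefficient is centred on zero. Nor is a paired test on arbitrarily paired, equal-sized arms biased; it is the wrong test.

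It would go too far to conclude that the trial is too small for Aim 1 because of this. The stated power reproduces under a baseline-adjusted analysis, so on this point the analysis text needs changing, not the sample size.

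**What to change.** - Replace the paired t-tests between modes with two-sample t-tests on change scores, with the rank-sum test as fallback, for the stratum comparisons. Keep paired tests, if wanted, only as within-arm description.
- Make the primary Aim 1 model an ANCOVA of the post-information score on the pre-information score, arm, language, literacy, and the interactions of language and literacy with arm, including the three-way term. Alternatively, keep the two-row mixed model, add arm-by-time and its language and literacy interactions, and name those as the parameters of interest. The first option matches the stated power.
- As a minor correction, replace the enrolment propensity with the propensity for arm assignment, or delete that weighting.

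The cost is wording only: both scores and all factors are already collected. The change should be recorded before outcomes are examined by arm.
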